#### Quality assurance

##### Data collection and management

There is a quality assurance officer responsible for ensuring all implementation and evaluation activities adhere to standard operating procedures. Quality assurance will include monitoring the process of obtaining consent, data collection, transfer of completed survey instruments, data management and the secure storage of study materials. In addition, field supervisors will monitor the survey administration undertaken by field workers and make frequent visits (at least once a week) to assess the quality of data collection and review completed questionnaires.

Only authorised staff with appropriate training will have access to the databases to perform data entry. All databases will be password protected. Each data form will be entered by two data entry clerks in a database of the same structure using two different computers. Entries will be compared for discrepancies using the Epi info 2000 data compare utility. Any discrepancies will be corrected by crosschecking against the corresponding original questionnaire. Checks (validation rules) will be implemented in different fields of the database. Data will also be queried electronically to ensure the correct data is entered under the correct variables for each section of the form/questionnaire. A log of all data changes will be kept. Questionnaires will be kept in a locked filing cabinet.

##### Independent verification of malaria tests conducted and test results

Reliance on providers register of malaria tests conducted and their interpretation of the test result may be a risk for data quality. For example, we are dependent on the providers' skills in conducting and interpreting the test results and the accuracy of their record-keeping. We will examine the accuracy of the register of malaria tests by comparing the patient reported data on whether they had a test with the register. We will also independently conduct RDT tests in a sub-sample of 5% of patients on exit that reported they were tested for malaria to determine the degree of consistency between the test result recorded by the provider and the test result conducted by the fieldworker. In addition, a sample of cases (both positive and negative) will be tested using PCR to check the sensitivity and specificity of both RDT and Microscopy. Quality assurance of the RDTs is beyond the scope of the study.

### Sample size

#### Patient exit survey

Sample size calculations are based on the primary outcome, the proportion of patients that receive treatment according to malaria treatment guidelines. Based on results from the formative research we expect that this will be 15% in the control arm (current practice) with a coefficient of variation (*k*) within stratum of 0.3.

To evaluate the effect of each of the intervention arms compared to current practice we have powered the study to detect a 15% increase over the control, from 15% to 30%, which was deemed to be the minimum increase for each of the interventions to be worthwhile. Using methods for stratified cluster randomised trials [33] and assuming k = 0.25 in the intervention arms, 7 clusters per arm and 100 patients per facility are required to detect this improvement with 80% power at a 5% significance level. With allowance for drop outs from the trial we propose 9 facilities per arm. A lower coefficient of variation was assumed in the intervention arms due to the shared training.

If both intervention arms prove to be significantly better than the control it is likely that the enhanced intervention will be better than the basic intervention and we expect a further 10% improvement in the primary outcome, to 40%. Therefore to determine whether or not the basic intervention should be recommended we wish to evaluate whether it is just as effective as (i.e. non-inferior to) the enhanced intervention. Assuming that the largest difference between the two intervention arms that would be considered unimportant is 10% (i.e. non-inferiority margin) then using methods for equivalence in cluster randomised trials [33] 17 clusters per intervention arm with 100 patients per cluster are required to have 80% power to demonstrate that the limit of a one-sided 95% confidence interval (CI) will be 10% or less. With allowance for drop outs from the trial we propose 19 clusters per arm.

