### Hypotheses

• Basic Intervention is more effective in improving the treatment and diagnosis of malaria (measured by adherence to malaria treatment guidelines) than current practice.

• Enhanced Intervention will be more effective in improving the treatment and diagnosis of malaria compared to current practice and compared to Basic Intervention.

• Basic Intervention is more cost-effective in improving the treatment and diagnosis of malaria compared to current practice.

• Enhanced Intervention is more effective and more costly compared to Basic Intervention.

The relationship between the study hypotheses and outcomes are summarised in Figure 1.

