### Data analysis

Initially an overall test of the null hypothesis that there are no differences between either of the intervention arms and the control will be performed to guard against over-interpretation of any significant effects from individual comparisons of each intervention with the control, particularly if there is no evidence of a difference for any of the intervention arms.

The effect of the two interventions compared with control will be analysed with methods appropriate for cluster randomised trials. Point estimates of the primary outcome will be calculated using the unweighted mean of the cluster summaries in each stratum. If the distribution of the summary measures in each study arm is skewed, a logarithmic transformation to the proportions will be considered. An overall estimate of the risk ratio will be obtained by taking a weighted average of the stratum-specific risk ratios where the weights are inversely proportional to the stratum-specific variances. 95% confidence intervals (CI) will be adjusted for observed between-cluster variance and formal hypothesis testing will be conducted using stratified t-tests. Adjustment for covariates, including patient and provider characteristics and knowledge, contextual factors and process factors, will be carried out using a two-stage process. In the first stage, a logistic regression model including stratum as a fixed effect and the covariates of interest, but excluding the intervention effect, will be fitted to calculate cluster-specific expected values. The ratio of observed and expected values will be computed to give the ratio-residual for each cluster. In the second stage, the above methods for estimating the RR and 95% CI and hypothesis testing are carried out with the cluster-level proportions replaced with the covariate-adjusted residuals [35].

Non-inferiority between the two intervention arms will be assessed using the same methods as described above but instead of the risk ratio the risk difference will be estimated. Inference will be based solely on one-sided 95% CIs (or equivalently 2-sided 90% CIs).

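### Enhanced versus basic training: the superiority hypothesis, the 10-point non-inferiority margin and the non-inferiority-only analysis do not fit together

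*Protocol article*

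**What the plan says.** **Objectives and Hypotheses.** Enhanced versus basic is the third comparison under the primary objective. The second hypothesis reads "Enhanced Intervention will be more effective in improving the treatment and diagnosis of malaria compared to current practice and compared to Basic Intervention".

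**Sample size, Patient exit survey.** Against control, "we have powered the study to detect a 15% increase over the control, from 15% to 30" per cent. For enhanced over basic, "we expect a further 10% improvement in the primary outcome, to 40" per cent. The text then turns to basic: "we wish to evaluate whether it is just as effective as (i.e. non-inferior to) the enhanced intervention". The margin follows: "the largest difference between the two intervention arms that would be considered unimportant is 10" per cent. The result is that "17 clusters per intervention arm with 100 patients per cluster are required" for 80% power with a one-sided 95% CI, raised to 19 per arm for drop-outs.

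**Data analysis.** The overall test and the risk-ratio analyses compare the interventions with control. For the two intervention arms the risk difference is estimated and non-inferiority is assessed: "Inference will be based solely on one-sided 95% CIs", described as equivalent to two-sided 90% CIs.

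**The concern.** Three parts of the plan answer different questions. The hypothesis says enhanced is better. The sample size section expects it to be better by 10 points, then classes a difference of that size as unimportant. The analysis section asks only whether basic can be shown to be less than 10 points worse.

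The consequence depends on which scenario is true. The 80% power describes a trial in which the two arms do equally well, which is not what the preceding sentences expect. If the expectation is right, the usual result will be that non-inferiority is not shown. That result does not separate a real benefit of enhanced training from imprecision, and the plan names no test that would. The comparison determines the size of both intervention arms, 38 of the 47 facilities, so the trial should be able to report a clear conclusion on it.

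**Working it through.** **Inputs (Sample size, Patient exit survey).** Coefficient of variation k = 0.25 in both intervention arms; m = 100 patients per facility; margin 10 points; one-sided 5%; 80% power; 17 clusters per arm, 19 after the drop-out allowance. Expected proportions are 30% (basic) and 40% (enhanced).

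**Formula.** Variance of a cluster proportion: v(p) = p(1 − p)/m + k²p². Clusters per arm: c = 1 + (z_α + z_β)² × [v(p_B) + v(p_E)] / D².

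- v(0.40) = 0.0024 + 0.0100 = 0.0124
- v(0.30) = 0.0021 + 0.005625 = 0.007725

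**Reproducing the stated 17 (non-inferiority).**

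- Both arms at 40%: (1.645 + 0.842)² × 0.0248 / 0.01 = 15.33; plus 1 = 16.33, rounded up to **17**, as stated.
- Both arms at 30%: 9.55 + 1 = 10.55, rounded up to 11.
- Both arms at 35%: 12.28 + 1 = 13.28, rounded up to 14.

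With the protocol's one-sided 5% and 80% power, equal arms at 40% gives the stated figure. The article does not state these proportions, so this is inferred.

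**Probability of declaring non-inferiority when the arms differ.** SE = √{[v(p_B) + v(p_E)]/c}. The probability comes from the noncentral t with 2c − 4 degrees of freedom (two strata) and noncentrality (0.10 − true gap)/SE. At c = 19:

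| Basic v enhanced | True gap | Probability |
|---|---|---|
| 40% v 40% | 0 | 86% |
| 37.5% v 40% | 2.5 points | 67% |
| 35% v 40% | 5 points | 41% |
| 30% v 40% | 10 points | 5% |

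At c = 17 the figures for gaps of 0, 5 and 10 points are 82%, 38% and 5%. In the last row the noncentrality is (0.10 − 0.10)/SE = 0, so the probability equals the one-sided 5% whatever the number of clusters, k or m.

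**Superiority of enhanced, two-sided 5%, 30% v 40%.** Variance sum 0.007725 + 0.0124 = 0.020125. Clusters: (1.960 + 0.842)² × 0.020125 / 0.01 = 15.80; plus 1 = 16.80, rounded up to 17. By the noncentral t:

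- c = 17: SE = √(0.020125/17) = 0.0344, power 80%
- c = 19: SE = √(0.020125/19) = 0.0325, power 85%

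**What the planned 90% CI would show.** At 30% v 40%, its lower limit for enhanced minus basic lies above zero in about 88% of trials at c = 17 and 91% at c = 19.

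**The case against.** Most of the other side's case is fair.

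- **The 5% is not lost power.** A reader might infer that the comparison has only 5% power. At 30% v 40% the non-inferiority null is true, on its boundary, so 5% is the type I error rate. If enhanced really is 10 points better, declining to call basic non-inferior is what the test is meant to do.
- **Sizing at zero difference is conventional.** The fault is that the assumption is unstated and sits beside a contrary expectation. The inference to 40% v 40% is also not unique, since a two-sided superiority calculation at 30% v 40% rounds up to 17 too. The article's one-sided non-inferiority wording favours the equal-arms reading.
- **The objective is not left unanswered.** A reader might infer that it is. The risk difference and its 90% CI are planned, and the Data analysis section plans an incremental cost-effectiveness ratio for each comparison. The interval would often exclude zero. But no inference is planned from that limit, and reading superiority from it would be a one-sided 5% test, less strict than the 95% CIs used against control.
- **An analysis of variance between the intervention arms is planned.** It concerns coverage estimates, which are not defined, and stands in the paragraph on secondary outcomes. It does not supply a superiority test on the primary outcome.
- **A full analysis plan will be agreed before analysis.** It is not shown and could add the test. The point is not that detail is absent: the protocol fixes the margin, the expectation and the word *solely*, so such an addition would conflict with it.
- **Asking whether the less resource-intensive training is good enough is legitimate.** This stands, and the non-inferiority question should stay.

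**Conclusion.** The point holds as a mismatch between hypothesis, margin and analysis. The same 10 points is both the expected gain and the largest unimportant difference, and the hypothesis that enhanced is better has no named test on the primary outcome. The quoted 80% power applies to equal arms at about 40%. At 19 clusters per arm the probability of showing non-inferiority falls to about 41% at a 5-point gap and 5% at the expected 10 points, and a failure to show it would not establish superiority.

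The 5% follows from the true difference equalling the margin and needs no other assumption. The remaining figures rest on k = 0.25, 100 patients per facility, two strata and a cluster-level t-test. The documents do not support the stronger readings that the trial is too small or that the comparison would yield nothing usable: 17 to 19 clusters per arm suffice for either question under its own assumption, and the estimate, interval and cost-effectiveness ratio would be reported. Comparisons with control are unaffected.

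**What to change.** **Sample size, Patient exit survey.** State that the 80% non-inferiority power assumes no true difference, with about 40% in both arms. Add the probability of showing non-inferiority at gaps of 5 and 10 points (about 41% and 5% at 19 clusters per arm). Reconcile the expected 10-point gain with calling 10 points unimportant, by justifying the margin or revising one of the two statements. Quote the superiority power for 30% v 40%: about 80% at 17 and 85% at 19 clusters per arm.

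**Data analysis.** Remove the restriction to the non-inferiority interval. Keep the 90% CI read against the 10-point margin, and add a prespecified two-sided 5% superiority test with a 95% CI for the enhanced-minus-basic risk difference.

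**Cost.** Wording only, with no extra facilities or patients. Data collection was under way when the article was written, but the analysis plan was still to be agreed before analysis, so the test could be prespecified there. The downside is a less favourable statement of non-inferiority power.

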#### Provider survey

The sample size calculations for the provider survey gives the anticipated level of precision for calculating the proportion of providers that know the treatment guidelines (i.e. report that parasitological testing is recommended and that ACTs are for confirmed cases of malaria). Based on our formative research we can assume 3-4 providers per facility, an intra-correlation coefficient (ICC) of 0.1, and an estimate of the primary outcome in each arm of 90%. With 9 facilities in the control arm and 19 facilities in each of the intervention arms this allows us to estimate the true primary outcome with ± 11.8% precision in the control arm and ± 7.7% precision in each of the intervention arms.

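### Two planning figures do not follow from their inputs: the provider precisions (±11.8% and ±7.7%) need different numbers of providers per facility, and 7 clusters per arm give about 89% to 94% power, not 80%

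*Protocol article*

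**What the plan says.** Under Sample size, Provider survey, the protocol article assumes "3-4 providers per facility, an intra-correlation coefficient (ICC) of 0.1, and an estimate of the primary outcome in each arm of 90" per cent. It continues "With 9 facilities in the control arm and 19 facilities in each of the intervention arms" and arrives at "11.8% precision in the control arm and ± 7.7% precision in each of the intervention arms". It gives one range of cluster sizes for all arms and names no confidence level.

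Under Sample size, Patient exit survey, the expected primary outcome is "15% in the control arm (current practice) with a coefficient of variation" of 0.3 within stratum. The aim is to "detect a 15% increase over the control, from 15% to 30" per cent. The text then says "assuming k = 0.25 in the intervention arms, 7 clusters per arm and 100 patients per facility are required"; the stated targets are a power of 80% and a significance level of 5%. The 7 is raised to 9 for drop-outs. The intervention arms are sized separately by a non-inferiority calculation, which gives 17 clusters per arm, raised to 19.

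**The concern.** Both figures are presented as results of listed inputs, so a reader should be able to recover them.

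For the provider survey, only the number of facilities differs between control and intervention arms. The ratio of the two half-widths is then fixed whatever the cluster size or ICC, and the printed pair does not have that ratio. In addition, 90% plus 11.8 points passes 100%.

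For the exit survey, the listed inputs lead to fewer than 7 clusters at 80% power, so either the power or one of the inputs is misreported.

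Provider knowledge supplies several secondary outcomes and enters the cost-effectiveness ratios, and the article promises a full analysis plan into which these figures could be copied. What is at stake is the accuracy of the planning statement, not the size of the trial.

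**Working it through.** **Provider survey.** Inputs (Sample size, Provider survey): p = 0.90, ICC = 0.1, m = 3 to 4 providers per facility, c = 9 (control) and 19 (each intervention arm). A 95% level is assumed.

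Half-width = 1.96 × √{p(1−p) × [1 + (m−1) × 0.1] / (c × m)}.

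| m | design effect | control, c = 9 | intervention, c = 19 |
|---|---|---|---|
| 3 | 1.20 | ±12.4 | ±8.5 |
| 3.5 | 1.25 | ±11.7 | ±8.1 |
| 4 | 1.30 | ±11.2 | ±7.7 |

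The plan's ±7.7 is reproduced at m = 4: 1.96 × √(0.09 × 1.3/76) = 7.69 points. At the same m the control figure is 1.96 × √(0.09 × 1.3/36) = 11.17, not 11.8.

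Solving for m gives 3.43 for ±11.8 and 3.99 for ±7.7. Allowing for rounding of the printed figures, the ranges are 3.39 to 3.47 and 3.91 to 4.06, which do not overlap.

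The ratio test needs neither m nor the ICC. At a common m the half-widths must differ by √(19/9) = 1.453. The stated ratio is 11.8/7.7 = 1.532, and the smallest ratio that rounding allows is 11.75/7.75 = 1.516. A 90% level and t quantiles (on clusters or on providers) do not recover the pair either. Eight control facilities with m = 4 come close at 11.85, but the text says 9.

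Upper limits: 90 + 11.8 = 101.8% (control) and 90 + 7.7 = 97.7% (intervention). As a bounded alternative, Wilson limits at m = 3.5 use effective sample sizes of 9 × 3.5/1.25 = 25.2 and 19 × 3.5/1.25 = 53.2. They are 72.6% to 96.8% and 79.1% to 95.5%.

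**Exit survey, superiority.** Inputs (Sample size, Patient exit survey): p0 = 0.15, p1 = 0.30, k0 = 0.3, k1 = 0.25, 100 patients per facility, 80% power, 5% significance (two-sided assumed).

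Clusters per arm = a + (z_α + z_β)² × [p0(1−p0)/100 + p1(1−p1)/100 + k0²p0² + k1²p1²] / (p1−p0)², where a is the small-sample term.

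- Variance sum: 0.001275 + 0.0021 + 0.002025 + 0.005625 = 0.011025.
- Core: (1.96 + 0.842)² × 0.011025/0.0225 = 3.85.
- With a = 1: 4.85, so 5 clusters. With a = 2: 5.85, so 6 clusters.
- Noncentral t: 5 clusters give 79.8% (8 df) or 75.9% (6 df, two strata), and 6 give 88.3% (10 df) or 86.4% (8 df). This also leads to 6.
- A one-sided 5% test has core 3.03 and again gives 5 or 6.

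Power with 7 clusters per arm: 93.8% (a = 1), 93.4% or 92.5% (noncentral t, 12 or 10 df), 89.2% (a = 2).

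Cross-check on the same section's 17 clusters: with 40% in both arms, k = 0.25, a 10-point margin and a one-sided 5% level, (1.645 + 0.842)² × 0.0248/0.01 = 15.33. Adding 1 gives 16.33, so 17. The a = 1 formula therefore reproduces the non-inferiority figure but not the 7.

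Inputs that do give 7 include 90% power with a = 1 (5.15 + 1 = 6.15), k = 0.3 in both arms with a = 2 (4.71 + 2 = 6.71), and a two-sided 2.5% level with a = 2 (4.66 + 2 = 6.66). None of these is the stated set.

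**The case against.** The strongest defence of the provider figures is that the text gives a range of 3 to 4, not one value, and that each figure alone falls inside what the range allows (±11.2 to ±12.4 and ±7.7 to ±8.5). That stands, so neither figure is impossible on its own. It does not rescue the pair, because the section states no arm-specific cluster size and rounding does not close the gap.

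A symmetric half-width is also a common planning device and does not commit the analysis to symmetric intervals. That stands too: the 101.8% shows that the approximation is strained at 90% with few clusters, not that an analysis method is wrong. A reader might infer that both intervals pass 100%. Only the control one does.

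On the exit survey, the cited methods source is not available here, and the small-sample term that was used is not stated. The match with 17 comes from a separate calculation and does not settle that term. A reader might therefore conclude that power at 7 clusters is definitely over 90%. The documents do not support that, since one reasonable correction gives 89.2%. They do support that it is well above 80% under every correction tried.

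A reader might also infer that the stated power conceals how small a difference the randomised 9 versus 19 facilities could detect. The article claims no power for that comparison. It explains openly where 9 and 19 come from, and it presents 15 points as the smallest worthwhile gain, not the smallest detectable one.

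**Conclusion.** The point holds as a minor inconsistency in two planning figures.

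- The precision pair cannot come from one cluster size: about 3.4 providers per facility in control against 4.0 in the intervention arms. Put on a common value, the control figure falls by about 0.6 points (at 4 providers) or the intervention figure rises by about 0.4 (at 3.5). The intervention figure sits at the favourable end of the stated range, but calling it wrong in isolation would go too far.
- Seven clusters per arm is one or two more than the stated inputs need for 80% power, and gives about 89% to 94%. The error is conservative. The 7 bears only on the control arm's 9 facilities, because the intervention arms are sized for non-inferiority.

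This rests on a 95% level for the precisions, a two-sided 5% test and the standard cluster-trial formula. The one-sided reading gives the same 5 to 6 clusters. No decision on design or analysis depends on either figure.

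**What to change.** In Sample size, Provider survey, state one number of providers per facility for all arms and recompute both figures. At 3.5 they are ±11.7 points (control) and ±8.1 points (each intervention arm), with ranges for 3 to 4 providers of ±12.4 to ±11.2 and ±8.5 to ±7.7. State the confidence level. Preferably give limits that stay below 100%, for example Wilson limits of 72.6% to 96.8% and 79.1% to 95.5% at 3.5 providers.

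In Sample size, Patient exit survey, either restate the power at 7 clusters per arm as about 90% (89% to 94% depending on the small-sample correction), or state the input that actually produced 7, such as 90% power or k = 0.3 in both arms. Say whether the 5% level is two-sided.

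The cost is a few restated figures. No facilities, patients, data collection or analyses change.
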